### Data collection and management

#### Survey design and measurements

A survey questionnaire will assess primary and secondary outcomes, along with selected covariates. The questionnaire will be developed in English and translated into Luo. The questionnaire will be refined with input from the CAC and pretested with 6–10 students to evaluate ease of comprehension, suitability of questions, and completion issues. Internal consistency of relevance scales (e.g., attitudes, stigma) will be assessed using Cronbach’s alpha.

The questionnaire will take up to 60 min to complete and will include questions about socio-demographics, reproductive and sexual health behavior, HIV testing, and HIV care. Stigma outcomes will be measured using three validated scales:Enacted, anticipated, and internalized stigma among HIV-positive students will be measured using the *Adolescents Living with HIV—Stigma Scale* [30].Courtesy stigma will be measured using the *Brief Stigma by Association Scale in HIV-affected students* [31].Perceived stigma will be measured using *Stewart’s 10-item subscale on felt-normative stigma towards PLHIV* in their community [32].

As intervention benefits may attenuate over time [35], we will examine sustainability of attitudinal change and stigma-associated change five months after the intervention has ended. Sexual risk, HIV testing frequency, and HIV status will be assessed by self-report.

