### Outcomes

Outcomes will include self-reported stigma-related measures and clinical measures. The primary outcomes are enacted, anticipated, and internalized stigma as measured using the *Adolescents Living with HIV—Stigma Scale* [30]. Secondary outcomes will include courtesy and perceived stigma measured using *Stewart et al.’s 10-item subscale* [31] and the *Brief Stigma by Association Scale* [32]. Secondary clinical outcomes will include HIV testing frequency among sexually active participants; and linkage to care, time to initiation of antiretroviral therapy (ART), ART adherence, and viral suppression, among participants living with HIV. Study outcomes will be assessed by independent research team members at baseline, following each crossover period (i.e., every 8 weeks), and 5-months after completion of the final intervention block.

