### Power calculation

Using the power and detectable-difference calculations for stepped-wedge cluster-randomized trials (91) (Stata 14.2), we calculated 98% power to detect a 20% reduction (i.e., an absolute risk difference of 12%) in the proportion of young people reporting a stigma endpoint (i.e., endorsing sufficient elements in the primary stigma measure) given a baseline proportion of 60% experiencing HIV-related stigma, a 5% two-tailed type I error rate, and an intra-cluster correlation coefficient (ICC) of 0.01. There is a lack of published ICC estimates in this setting. Prior work in sub-Saharan Africa and rural Uganda found that 50% of participants experienced stigma in some form [33]. Given our team’s prior experience working among young people in areas recovering from conflict, we have assumed a higher baseline proportion of 60% to have experienced HIV-related stigma. We targeted a total cluster size of 12, with four schools (two primary and two secondary) grouped to crossover from control to intervention at three specified crossover points. We estimate that there will be 150 students enrolled per school across eligible grade levels. Assuming a 50% participation rate after attrition, we estimate that the evaluation will reach 75 students per school for a total sample of *n*=900 who will complete the surveys at the end of the final data collection period﻿ [34].

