#### Analysis of survey data

Descriptive statistics will be used to assess balance between clusters and to describe schools relative to the required sample size at each timepoint, socio-demographic characteristics, and primary/secondary outcomes. Main analyses will use linear mixed effect models (LMEM) or generalized linear mixed effect models (GLMEM) to assess the intervention effect. LMEM will be used for continuous outcomes that approach normality and GLMEM will be used for binary and other types of outcomes. Normality will be assessed using model residuals and outliers by Cook’s distance, leverage, and residuals. Time in weeks from the beginning of the trial, time in weeks centered at the beginning of the intervention, time in weeks from the beginning of school semesters, and blocks will be specified as fixed effects. The multilevel structure will be defined by assessments within participants as level one, participants as level two, and schools as level three. Schools and participants within schools will be specified as random effects. Main analyses will follow an intention-to-treat approach, with clusters analyzed as per the original treatment assignment. Sensitivity analyses will be performed to assess bias arising from attrition. A significance level of 0.05 will be used in all statistical tests. Analyses will be conducted in SAS v9.4.

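### The 5-month assessment has no concurrent control and falls after delivery has ended; it should be kept out of the main effect model and reported as uncontrolled follow-up

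*Protocol article*

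**What the plan says.** Under Study design, three blocks of four schools cross over within a 32-week trial and receive 24, 16 or 8 weeks of intervention. Under Outcomes, assessments are at baseline, every 8 weeks, "and 5-months after completion of the final intervention block". The section on survey design and measurements gives the purpose of the last one. Noting that benefits may attenuate, it says "we will examine sustainability of attitudinal change and stigma-associated change five months after the intervention has ended".

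Under Analysis of survey data, the fixed effects are weeks from the start of the trial, weeks centred at the start of the intervention, weeks from the start of school semesters, and blocks. "The multilevel structure will be defined by assessments within participants as level one", with participants and schools above them. That section names no separate model, contrast or exclusion for the 5-month assessment.

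**The concern.** A stepped-wedge trial identifies its effect at times when some schools have crossed over and others have not. The 5-month wave offers no such contrast, and it is also the only wave at which the intervention is no longer being delivered. Two things follow.

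First, what it shows about sustainability is a before-after comparison. Second, if it is pooled with the trial waves under a straight-line time trend, it helps to set that trend. Any fading is then read partly as secular change, and the intervention coefficient shifts to compensate. The protocol itself expects fading, so this is not a remote case. The main effect estimate and the reading of the follow-up are both at stake.

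**Working it through.** **Inputs from the protocol article.** Study design: starts at weeks 8, 16 and 24, four schools each. Outcomes: waves at weeks 0, 8, 16, 24 and 32, then 5 months later (about week 53.7). Power calculation: 60% against 48%, "an intra-cluster correlation coefficient (ICC) of 0.01", 75 students per school, and 12 schools "with four schools (two primary and two secondary) grouped to crossover from control to intervention at three specified crossover points".

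**Step 1: the stated power, without the 5-month wave.** Hussey-Hughes variance with I = 12 schools and T = 4 periods:

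Var = I·s²(s² + T·t²) / [(I·U − W)s² + (U² + I·T·U − T·W − I·V)t²]

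- Exposed schools per period are 0, 4, 8, 12. So U = 24, W = 16 + 64 + 144 = 224, and V = 4·9 + 4·4 + 4·1 = 56.
- At the mean proportion 0.54, the variance is 0.54 × 0.46 = 0.2484. So s² = 0.2484/75 = 0.003312 and t² = 0.2484 × 0.01/0.99 = 0.002509.
- Numerator: 12 × 0.003312 × (0.003312 + 4 × 0.002509) = 0.0005305. Denominator: 64 × 0.003312 + 160 × 0.002509 = 0.6134.
- SE = √(0.0005305/0.6134) = 0.0294. Power = Φ(0.12/0.0294 − 1.96) = 98.3%, against 98% stated.

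The planned power therefore does not need the 5-month wave.

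**Step 2: controls at each wave.**

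| Wave | Control schools | Exposed schools |
|---|---|---|
| Week 0 | 12 | 0 |
| Week 8 | 12 | 0 |
| Week 16 | 8 | 4 |
| Week 24 | 4 | 8 |
| Week 32 | 0 | 12 |
| 5 months | 0 | 12 |

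With a free effect for each wave, a separate 5-month intervention effect cannot be estimated: the design matrix has rank 9 for 10 columns. Week 32 has no control either, but it is a planned step during delivery and is part of the power calculation.

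At 5 months, weeks since the start would read 53.7 − 8, − 16 and − 24, or about 46, 38 and 30. Delivery lasted 24, 16 and 8.

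**Step 3: expected estimates.** These are generalised least squares projections on school-wave means, on the risk-difference scale, with block fixed effects and random school and participant effects. The true effect is −12 points during delivery, with no secular trend.

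Assumptions not in the protocol:
- Week is linear or categorical, as shown.
- The intervention term is either 0/1 or exposure weeks set to 0 before the start. Left untruncated, that term equals trial week minus a block constant, so it is collinear with week and block whichever waves are used. That is a separate problem.
- The share of the effect retained at 5 months is 100%, 50% or 0%.
- The semester term is left out.
- Within-participant correlation is 0, 0.3 or 0.5; for the 0/1 term this does not change the estimates. The exposure-week slopes were rerun at 0.3 only.

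| Intervention term and time | Weeks 0-32 only | With wave, all retained | Half lost | All lost |
|---|---|---|---|---|
| 0/1, linear week | −12.0 | −12.0 | −14.3 | −16.6 |
| 0/1, categorical wave | −12.0 | −12.0 | −12.0 | −12.0 |
| Exposure weeks, linear week (slope per 8 weeks) | −3.6 | +0.3 | +1.7 | +3.1 |
| Exposure weeks, categorical wave (slope per 8 weeks) | −3.75 | −2.35 | −2.35 | −2.35 |

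In the first row, a rebound at 5 months tilts the fitted line upward, so the 0/1 term must fall further to fit the exposed waves. In the third row the sign has changed even with nothing lost, because a slope is being fitted to a step effect.

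**Step 4: calendar change gives the same distortion.** All use linear week and a 0/1 term with the wave included.
- Effect retained, with a 6-point secular decline that stops at week 32: −13.6.
- Effect retained, with a 6-point fall in all schools at 5 months only: −9.7.
- Half the effect lost, with that same 6-point fall: −12.0, exactly as with full retention and no calendar change.

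In the last case the two explanations cannot be told apart.

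**Step 5: precision.** With linear week, a 0/1 term and participant correlation 0.3, adding the wave cuts the SE from 0.0231 to 0.0194, about 16%. Most of that gain is bought by the straight-line assumption; with categorical waves the SE falls only from 0.0247 to 0.0239.

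**The case against.** The strongest reply is that much of this rests on silence. The analysis section does not use the word linear, lists no 0/1 intervention term, and does not say that all six waves enter one model. The statement on levels describes nesting, not which waves are used. A full protocol or analysis plan, not shown, could exclude the wave or use categorical time. This stands as far as the bias figures go: they are conditional, and the direction depends on the coding. It does not touch the missing control, which is a feature of the design that no analysis plan can change.

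A reader might infer that the main effect will be exaggerated. The documents do not support that: with exposure weeks as the intervention term the apparent benefit vanishes or reverses, and with categorical waves and a 0/1 term there is no bias.

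A reader might also infer that the trial intends to claim sustained benefit. The protocol says only that it will examine sustainability, and its objectives list no sustainability effect. Collecting such a wave is legitimate and, in a design where every school crosses over, it is bound to be uncontrolled.

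Some threats are partly met. The model has a term for time within the semester, sensitivity analyses for attrition are planned, and absent students will be followed up. These help, but none supplies a comparison group at 5 months.

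**Conclusion.** The point holds in two parts of different strength. That the 5-month wave has no concurrent control follows from the design alone, so change after week 32 is uncontrolled whatever model is used. That the wave can distort the main estimate is conditional on including it with week as a linear term. Then a true 12-point reduction becomes 14.3 points with half the effect lost and 16.6 with all lost under a 0/1 term, and under truncated exposure weeks the slope per 8 weeks moves from −3.6 to between +0.3 and +3.1. These sizes illustrate the sensitivity under assumed coding and retention; they are not predictions of the trial's result. Weeks 0 to 32 alone with a 0/1 term give −12.0 whatever happens later.

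**What to change.** State in the analysis section that the main effect model uses the assessments at weeks 0 to 32 only, preferably with categorical wave effects. Categorical waves alone are not enough if exposure weeks remain the intervention term, as the last row of the table in step 3 shows.

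Report the 5-month assessment in a separate analysis, as within-school change from week 32. Label it uncontrolled and draw no causal conclusion on sustainability from it.

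If the three blocks are compared at 5 months, label that a randomised comparison of 24, 16 and 8 weeks of exposure, with four schools each. It is not a test of sustainability: equal full retention and equal full loss in every block would both give a zero contrast.

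The cost is a weaker statement on sustainability. The change is to wording only; data collection stays as planned and the stated power is unaffected.

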## Background

Children and adolescents growing up with HIV infection or those living with parents or caregivers who live with HIV or AIDS experience various forms of stigma. Stigma refers to attitudes and beliefs that lead people to reject, avoid, or fear those they perceive as different and can lead to mistreatment and reduced access to power and opportunities [1]. HIV-related stigma continues to negatively impact HIV prevention, treatment, and care. For instance, HIV-related stigma has been associated with reduced uptake of voluntary counseling and testing [2], reduced likelihood of HIV status disclosure [3], and poses a significant barrier to antiretroviral therapy (ART) medication adherence, contributing to high rates of HIV mortality, especially in sub-Saharan Africa [4, 5]. Additionally, HIV stigma contributes to mental health issues in children and adolescents, such as anxiety and depression [6]. It may lead to school drop-out due to bullying, discrimination by peers and teachers and suicidal ideation [7]. As a result, young people face the dual burden of physical illness from living with the HIV virus and psychosocial distress resulting from stigma and discrimination.

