#### Administrative health data

In partnership with TASO and community health clinics, health records will be used to assess clinical outcomes, including HIV status, date of confirmed diagnosis, time of ART initiation, viral suppression, and comorbid medical conditions. Data will be anonymized by sharing the unique Study ID file (linked to identifiers) with TASO, then receiving in return, data linked with the study ID stripped of all identifiers. These data will be linked by study ID within our de-identified dataset and remain confidential and anonymous. All data will be securely stored on a password-protected cloud-based platform, with access limited to approved members of the research team.

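### The primary outcomes come from HIV-positive students, but group membership is not fixed before exposure; if it follows self-report at each survey, it can shift with the intervention and bias the effect

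*Protocol article*

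**What the plan says.** Protocol article, Outcomes: "The primary outcomes are enacted, anticipated, and internalized stigma as measured using the" Adolescents Living with HIV—Stigma Scale. Assessments are at baseline, after each 8-week period, and five months after the final block.

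Survey design and measurements restricts that scale to one group: "Enacted, anticipated, and internalized stigma among HIV-positive students will be measured using the" same scale. The section ends by naming the source of status in the survey: "Sexual risk, HIV testing frequency, and HIV status will be assessed by self-report".

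Administrative health data gives a second source: "health records will be used to assess clinical outcomes, including HIV status, date of confirmed diagnosis, time of ART initiation, viral suppression". The records are joined to the survey file: "These data will be linked by study ID within our de-identified dataset and remain confidential and anonymous". Their stated purpose is the clinical outcomes; the stigma outcomes are not mentioned there.

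Background associates HIV stigma with "reduced likelihood of HIV status disclosure" and "reduced uptake of voluntary counseling and testing".

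Analysis of survey data specifies mixed models with random effects for schools and for participants within schools. Its intention-to-treat statement concerns clusters, which are kept in their assigned sequence. Its sensitivity analyses concern attrition.

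**The concern.** A student supplies primary data only if counted as HIV-positive. On the plain reading of the survey section, that depends on an answer the student gives in the survey. By the protocol's own account stigma makes such disclosure less likely, and the intervention aims to reduce stigma. Testing is a second route into the group, and HIV testing frequency is itself a secondary outcome.

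In a stepped wedge the exposed observations come later than the control observations in the same schools. A change in who reports being HIV-positive therefore lines up with the change in condition. If students who had concealed their status begin to report it after crossover, and they are the more stigmatised, the exposed periods contain a more stigmatised mix even when no individual has changed. A real reduction could be hidden, or a null effect could look like harm.

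Randomisation of schools does not protect against this, because the selection happens after exposure. Analysing clusters as assigned does not fix which students are in the set, and attrition analyses look at students who leave, not at those who enter.

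**Working it through.** **1. The plan's own figure.** Power calculation targets a 20% relative fall from 60%: 0.60 × 0.20 = 0.12, so 60% to 48%. The Hussey–Hughes stepped-wedge variance, with 12 schools, four periods, four schools crossing per step, 75 students per school per period, ICC 0.01 and two-sided 5%, gives 98.3% to 98.7% power, depending on the variance form and ICC definition. This agrees with the stated 98%. That calculation takes group membership as given, so it does not bear on this point. Only the 12-point target is used below.

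**2. Inputs not in the documents (assumed).** Let p be the true proportion stigmatised among HIV-positive students, a the probability that a stigmatised student reports HIV-positive status, and b the same for a non-stigmatised student. I take p = 0.60 (the protocol's planning value, applied here to HIV-positive students) and b = 0.80 throughout. For a, the main case is 0.50 before and 0.70 after crossover, with other values as a range.

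**3. Formula.** Observed proportion stigmatised among reporters = p·a / [p·a + (1 − p)·b].

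**4. Main case, no true effect.**
- Before: 0.60 × 0.50 / (0.60 × 0.50 + 0.40 × 0.80) = 0.30 / 0.62 = 48.4%
- After: 0.60 × 0.70 / (0.60 × 0.70 + 0.40 × 0.80) = 0.42 / 0.74 = 56.8%
- Spurious change: +8.4 points

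With a true fall to p = 0.48: 0.336 / (0.336 + 0.416) = 44.7%, so the observed change is −3.7 instead of −12 points.

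**5. Range of assumed shifts in a (simple before–after contrast).**

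| a before → after | Observed change, no true effect | Observed change, true −12 |
|---|---|---|
| 0.7 → 0.8 | +3.2 | −8.8 |
| 0.5 → 0.6 | +4.6 | −7.5 |
| 0.5 → 0.7 | +8.4 | −3.7 |
| 0.3 → 0.5 | +12.4 | +0.6 |

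**6. Direction.** Swap the roles: stigmatised students report at 0.80 throughout, non-stigmatised students at 0.50 then 0.70. Before: 0.48 / (0.48 + 0.20) = 70.6%. After: 0.48 / (0.48 + 0.28) = 63.2%. The spurious change is −7.4 points, so the sign depends on who the new disclosers are.

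**7. Effect of the planned model.** The planned participant random effect moves the estimate towards within-student comparison, which step 5 ignores. Stepped-wedge data were simulated with no true effect and the main-case rates, and fitted with a student random intercept. How disclosure is carried between surveys and how stable stigma is within a student were both varied.

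| Who is in the set | Approximate bias (points) |
|---|---|
| Reporters at each survey, decision made afresh each time | +4 to +8 |
| Reporters at each survey, decision driven by a stable student trait | +2 to +9 |
| Reporters at each survey, once disclosed always disclosed | 0 to +2 |
| Baseline reporters, kept throughout | 0 (within about 1) |

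The ranges come from few replicates and are approximate.

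**8. Students lost by fixing the set at baseline.** Reporters rise from 62% to 74% of HIV-positive students in the main case. At least (0.74 − 0.62) / 0.74 = 16% of post-crossover reporters are then new.

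**The case against.** The strongest reply is that the protocol never says self-report defines the primary analysis set, nor that students are reclassified at each survey. It lists status as a survey item and also obtains status and diagnosis date from linked records, which could define the group independently of disclosure. Which source and date define an analysis set is often left to the full protocol or SAP, and this is a condensed article. This stands in part: a reader might infer that the protocol has adopted wave-by-wave self-report as its rule, and the text does not go that far. But the records are named for clinical outcomes only and cover only students diagnosed at and known to those clinics. The matter also reaches beyond analysis wording. If the scale is given only to students who report HIV-positive status on the day, data from those not asked cannot be recovered by a later plan.

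A second reply is that the larger figures come from unfavourable assumptions. This stands: the disclosure rates are assumed, and if students keep disclosing once they have done so, the bias is close to nil.

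A third is that the direction is uncertain. The Background reports a general association between stigma and disclosure and does not address answers in a research survey, and step 6 shows the sign can reverse. This stands too.

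A fourth is that fixing the set by baseline self-report still leaves out students who conceal their status then. That is true, but it limits to whom the result applies; it does not let exposure alter the comparison.

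**Conclusion.** The point holds as a risk that the protocol leaves open and can close cheaply. The primary outcomes are restricted to HIV-positive students, status in the repeated survey is self-reported, a second source is given without a stated role for the primary outcomes, and no section fixes membership before exposure. If membership follows each survey's answer, the effect estimate can be biased, probably towards masking a benefit if new disclosers are the more stigmatised.

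Under the main-case rates and no true effect, the simulated bias runs from about 0 to 9 points against the 12-point target, and nearly vanishes when the set is fixed at baseline. These figures illustrate scale only; neither size nor direction can be derived from the documents. A reader might infer that the trial will be biased against the intervention by some 8 points. That is not supported: it needs both the assumed rates and disclosure that does not persist. The change is worth making, with medium confidence.

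**What to change.** State the following in the protocol before any school crosses over:

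- The primary analysis set is the students who report HIV-positive status at the baseline survey.
- They remain in the set and are offered the scale at every later survey, whatever they then answer on status.
- Students who first disclose or are diagnosed later are analysed separately, and a sensitivity analysis includes all reporters.
- The linked clinic diagnosis date is used to check the baseline set and to describe students with a recorded diagnosis who did not report it.

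Cost: late disclosers leave the primary set (about 16% or more of post-crossover reporters under the main-case assumptions), which reduces precision. A questionnaire routing rule is needed so that baseline members still receive the scale. The result applies to students willing to disclose at baseline, which should be said when it is reported. Otherwise the change uses data already planned.
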